### Health economics analysis

An economic evaluation would be an integral component of a future full trial and would assess the cost-effectiveness of tailored physiotherapy rehabilitation after rTHA compared with usual care, taking an 8-month (within trial) time horizon. The main outcome measure would be quality-adjusted life years, estimated using EQ-5D-5L.

In this feasibility study, the health economics component aims to test the practicality of collecting resource use and outcome data. We will take an NHS and personal social services perspective but will also collect data to assess whether there are substantial costs to patients and their families and whether a wider perspective should be considered in the full trial. Resource use will be recorded from the first physiotherapy appointment, with intervention-related data captured in trial case report forms and other health, social care and family support costs collected via participant resource use diaries at 4 and 8 months postoperatively. Participants will complete the EQ-5D-5L at baseline at 4 and 8 months postoperatively. For each time point, the proportion of participants followed up and data completeness for resource use and outcomes will be reported descriptively.

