### 3fRandomisation and allocation concealment

After the participants have undergone rTHA, the research clinician will re-assess their eligibility to participate. Participants may become ineligible if they require a further revision surgery or if their status and/or discharge destination has changed and impacts participation in outpatient physiotherapy. Eligible patients will be randomised by an unblinded research team member in a 1:1 ratio between the intervention and usual care groups using a web-based centralised randomisation database (SealedEnvelope), which will be managed by the trial manager. Stratified permuted block randomisation will be used, with stratification by sex and site. Blocks will be of random sizes. The statistician will oversee the allocation sequence produced by SealedEnvelope; no other members of the team will have access to it. By the nature of the intervention, patients and clinicians cannot be blinded to treatment once allocation has occurred. The research clinician collecting data from follow-up research visits will be blinded to treatment allocation. Additionally, data analysis will be conducted in a blinded fashion. Participants from both arms will complete the standard postoperative care pathway before being allocated to the treatment arm they were randomised to and scheduled for an outpatient physiotherapy appointment approximately 2–4 weeks post-operatively.

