### Data collection

Feasibility data will be collected during screening, recruitment, eligibility re-assessment and randomisation, during the 12- week intervention period, at 4 months postoperative, at 5- and 7-months postoperative for the THRIVE programme arm, and at 8 months postoperative. Outcome measures will be collected at three timepoints: baseline (preoperative), 4 months postoperative and 8 months postoperative (table 3). Schedule of study procedures. Follow-up questionnaires at 4 and 8 months will be posted to participants who do not attend the in-clinic follow-up research visit. Information from Protocol Deviation forms will be collected ad hoc and patterns and frequencies of deviations will be investigated. Qualitative interviews will be conducted with participants following completion of their intervention. Qualitative interviews with treating clinicians from the THRIVE programme arm will be conducted after they have completed all treatments for all participants.

**Table 3 T3:** Schedule of study procedures

Procedures	Pre-enrolment	Preoperative baseline	Postoperative		4 months follow-up	8 months follow-up	Post-intervention
	Screening	Visit 1	After operation	Intervention period	Visit 2	Visit 3	Qualitative interviews
Potential participant identification and screening	x						
Provision of PIS	x						
Eligibility assessment	x		x				
Informed consent		x					
Outcome questionnaire completion		x			x	x	
Physical assessment by research staff		x			x	x	
Randomisation			x				
Letter sent to GP informing study involvement			x				
Referral to physiotherapy (based on allocated arm)			x				
Trial interventions delivered				x			
Treatment log completed by physiotherapist (THRIVE intervention)				x			
Treatment log completed by physiotherapist (usual care)				x			
Home exercise diary (THRIVE intervention)				x			
Healthcare resource use and family social support diary				x	x	x	
Follow-up phone calls for THRIVE intervention				x			
Adverse events recorded				x	x	x	
Qualitative interviews with selected sample							x

GP, general practitioner; PIS, patient information sheet; THRIVE, tailored physiotherapy rehabilitation.

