The outcome assessments, including patient-reported outcome measures and performance-based measures, will be reported in a descriptive fashion, with no formal assessment of treatment effect between groups since this is a feasibility study. We will summarise outcomes overall and in each group. Completeness and variability of the outcome measures will be used together as a guide to help determine the best outcome for a future main study. We will visualise the change in outcomes over time within groups using plots. All analyses will follow intention-to-treat principles. We will report the amount of missing data for each outcome and summarise patterns of missingness.

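### Resource-use recording starts at the first physiotherapy appointment, so the start depends on attendance after randomisation and does not fit the 8-month evaluation it is meant to rehearse

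*Protocol article*

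**What the plan says.** All references are to the protocol article.

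- **Start of costing.** Health economics analysis: "Resource use will be recorded from the first physiotherapy appointment". Intervention data come from case report forms. Other health, social care and family support costs come from participant diaries collected at 4 and 8 months after surgery.
- **Order of events.** Randomisation and allocation concealment: "After the participants have undergone rTHA, the research clinician will re-assess their eligibility to participate". Those still eligible are then randomised, and later "scheduled for an outpatient physiotherapy appointment approximately 2–4 weeks post-operatively". Table 3 agrees: randomisation and referral stand in the after-operation column, while the resource diary first appears in the intervention-period column.
- **Utility measurement.** Health economics analysis: "Participants will complete the EQ-5D-5L at baseline at 4 and 8 months postoperatively". Data collection gives the three time points as "baseline (preoperative), 4 months postoperative and 8 months postoperative".
- **The evaluation being prepared.** For a future full trial, the economic evaluation is described as "taking an 8-month (within trial) time horizon", and "The main outcome measure would be quality-adjusted life years, estimated using EQ-5D-5L". In the present study the economic component only tests whether the data can be collected in practice, and it reports follow-up and completeness descriptively.
- **Analysis principle.** Statistical analysis plan section: "All analyses will follow intention-to-treat principles".

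**The concern.** In a randomised comparison of costs, the clock should start at a point that every randomised participant reaches and that allocation cannot influence. The first physiotherapy appointment meets neither condition. It comes after allocation, and reaching it depends on the participant attending and on the clinic offering a slot. A participant who is randomised but never attends has no start date under the stated rule, which sits badly with intention-to-treat.

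The start could also shift by arm. Different physiotherapists deliver the two programmes. The first THRIVE session must be in person, whereas usual care may be remote. At one site, out-of-area participants can have usual care from a community provider. If waits differed for such reasons, the cost windows would differ in length between arms.

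The two halves of the future cost-effectiveness ratio would also cover different periods: QALYs from a preoperative baseline to 8 months after surgery, costs from a floating date some weeks after surgery. The unrecorded stretch is the one soonest after the operation.

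What is at stake is the feasibility answer. If the rehearsed window cannot serve the definitive analysis, its completeness figures describe a procedure that would have to be changed.

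**Working it through.** The plan gives no figure for this point and makes no formal power calculation, so there is nothing of its own to reproduce. The check is timeline arithmetic.

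**Inputs from the document:** horizon 8 months; first appointment about 2 to 4 weeks after surgery; at least 60 participants. **Not given:** the date of randomisation relative to surgery, the interval from baseline EQ-5D-5L to surgery, and the share who never attend.

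**1. Unrecorded share of the postoperative horizon.**
Horizon in weeks = 8 × 365.25 / 12 / 7 = 34.8.
Unrecorded share = weeks from surgery to first appointment / 34.8.

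| First appointment | Unrecorded share of 8 months | Recorded weeks | Unrecorded share of first 4 months (17.4 weeks) |
|---|---|---|---|
| 2 weeks | 2 / 34.8 = 5.7% | 32.8 | 11.5% |
| 3 weeks | 3 / 34.8 = 8.6% | 31.8 | 17.2% |
| 4 weeks | 4 / 34.8 = 11.5% | 30.8 | 23.0% |

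The share rises if the appointment slips beyond 4 weeks. The interval before surgery comes on top, but its length is not stated.

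**2. Participants with no defined start.** The document gives no non-attendance rate. Expected number among 60 = 60 × p, with p assumed:

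- p = 0%: 0
- p = 2%: 1.2
- p = 5%: 3
- p = 10%: 6
- p = 15%: 9

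**3. Which part can differ by arm.** Split the gap into surgery to randomisation and randomisation to first appointment. The first part precedes allocation, so its costs are balanced between arms in expectation. Only the second part can differ by arm, and it is at most about 4 weeks if scheduling holds.

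**4. How much a start at randomisation recovers.** If randomisation falls d weeks after surgery, the recovered share is (appointment week − d) / 34.8 and d / 34.8 remains. As an illustration, assume d = 1. Recovery is then 1 / 34.8 = 2.9% for an appointment at 2 weeks and 3 / 34.8 = 8.6% for one at 4 weeks, with 2.9% remaining in both cases. The true split cannot be computed because d is not stated.

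**The case against.** The strongest reply is that nothing in this trial is affected. The QALY evaluation belongs to a later study, the present economic component is descriptive, and the start date could be revised before the full trial. It is neither a primary objective nor a named progression criterion. This stands as to bias: a reader might infer that mismatched costs and QALYs distort a result here, but none is compared. It does not remove the point, because rehearsing the data collection is the stated purpose of the component.

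Two further inferences are tempting and not supported. One is that data from non-attenders would be lost. Diaries are due at 4 and 8 months after surgery, which does not hinge on attending physiotherapy, and the full protocol, not shown here, may say how such cases are handled. The text supports only that their start is undefined. The other is that completeness would be judged on attenders alone. The article says no such thing, and its intention-to-treat statement and promised reporting of missing data point the other way.

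The arm difference is also only a possibility. Both arms have the same 2 to 4 week target and the same preceding care pathway, and no text indicates unequal waits. Non-attendance may be low, since patients whose changed status or discharge destination affects outpatient physiotherapy can be found ineligible before randomisation.

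Finally, starting at randomisation does not align costs fully with EQ-5D-5L. That is correct, and the remaining gaps need to be stated.

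**Conclusion.** The point holds as a design weakness in the procedure being tested. It rests on a rule the article states, not on a detail left to another document. The start of costing is attendance-dependent, comes after randomisation, is undefined for a randomised non-attender, and falls later than the start of the EQ-5D-5L period.

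The size is 5.7% to 11.5% of the 8 postoperative months, if appointments keep to schedule. The part that could differ by arm is smaller, by an amount that depends on the unstated date of randomisation. The number of participants without a start date is unknown; the 0 to 9 shown above rests wholly on assumed rates of 0% to 15%.

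No result of this feasibility study is biased. The change is still worth making, because it is cheap and makes the tested window one that an intention-to-treat cost analysis could use.

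**What to change.** 1. Start resource-use recording at the date of randomisation for every randomised participant, regardless of attendance.
2. Issue the diary at that point, and word the 4-month form to ask about the time since randomisation.
3. Report resource-use completeness at each time point with all randomised participants in each arm as the denominator. This makes explicit what the intention-to-treat statement already suggests.
4. State that two intervals remain uncosted: preoperative EQ-5D-5L to surgery, and surgery to randomisation. Note that costs in the second are balanced between arms in expectation.

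The cost is a changed start date on the diary and case report form, and up to about 2 to 4 more weeks of recording or recall for participants.

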### Safety reporting

The principal investigators are responsible for assessing all adverse events (AEs) and categorising seriousness, expectedness and relatedness. AEs will be defined and reported according to Good Clinical Practice guidelines.

### Embedded qualitative study

The qualitative study will include trial participants and physiotherapists and aims to explore their experience within the trial and understand measures to improve the delivery of a future trial.

#### Qualitative study design

Semi-structured interviews will be conducted by experienced qualitative researchers following completion of participation in the study. Analysis will follow the steps of Braun and Clarke’s reflexive thematic analysis.^46^

#### Sampling and recruitment

Patient participants will be purposefully sampled to include participants from a range of trial sites, of both sexes, with different indications for surgery and from a range of socio-economic contexts to gather a range of perspectives. Our sampling strategy will be influenced by the principles of information power that consider the aim of the study, sample specificity, use of established theory, quality of dialogue and analysis strategy, which is compatible with reflexive thematic analysis. Participants will be recruited from the pool of trial participants who have consented to be contacted about the qualitative study. Potential participants for the qualitative studies will be provided a PIS for the qualitative study and given time to consider participation.

#### Interview data collection and analysis

All participants will be asked to give their informed consent for this qualitative study before their interview. Interviews will be conducted by an experienced qualitative researcher within 4 weeks of participants’ final contact with a physiotherapist as part of the trial. We will collect data via semi-structured interviews conducted in person or remotely (online supplementary files: interview guides). We will record the interviews, then transcribe and de-identify transcripts. We will analyse the data using reflective thematic analysis.^46^

### Study management

A core team comprising the trial manager and chief investigators will be responsible for overseeing day-to-day study management and will meet at least once a fortnight. A trial management group (TMG) composed of the study co-applicants and our patient collaborator will meet four times per year aligning with study milestones. A trial steering committee (TSC) will be led by an independent chair and consist of three external members including an expert clinician, trialist and statistician. The group will meet two to three times per year. As this is a feasibility study, a data monitoring committee was not deemed necessary. Any data queries regarding quality and completeness will be directed to the TSC.

### Patient and public involvement

We have a patient and public involvement and engagement (PPIE) group composed of patients with lived experience. During the development of the interventions and trial design, we consulted four patients in the group and one of their carers. Their feedback led to changes in our protocol, for example, we altered our physiotherapy follow-up delivery mode to ensure remote visits were an option. One member of the group serves as our patient collaborator in the TMG. The PPIE group will have ongoing input throughout the duration of the study, including study conduct and data interpretation, and importantly during dissemination.

### Trial status

Recruitment commenced on 3 September 2025. We have opened four sites. Current trial protocol (version 4.0) can be accessed at https://www.ouh.nhs.uk/media/hsofchhk/thrive-protocol.pdf.

### Trial governance

The trial is sponsored by Oxford University Hospitals NHS Foundation Trust. The sponsor has no role in the design of the study, data collection, analysis, interpretation or writing of the manuscript.

### Ethics and dissemination

A UK Research Ethics Committee has approved this study (West of Scotland REC 25/WS/0080). All participants will provide their informed consent to participate in the study. The study will investigate the feasibility of conducting this trial and will also examine closely the practical, operational and safety barriers that arise. This is a diverse clinical population, with high healthcare utilisation, and many revision operations are performed at regional hubs. Specialist referral pathways might be barriers for recruitment since outpatient physiotherapy is delivered at the surgical centre where we can ensure expertise and adequately experienced musculoskeletal physiotherapists. At one study site, we are trialling the hub-and-spoke model. Participants who live ‘out-of-area’ can receive their standardised usual care from their local community provider. This will allow us to understand if the model has the potential to increase recruitment, decrease clinical load on the secondary care centre, and if participants value receiving physiotherapy more locally. As we analyse our primary outcomes, which are recruitment and retention rates, we will focus on these potential issues and probe them in the qualitative interview study.

Trial results will be reported in the trial registry, published in an open-access academic journal, presented at relevant physiotherapy and orthopaedic conferences and shared in an accessible summary with the trial participants. The final report will detail amendments to the study protocol. The final manuscript will be reported according to the^47^ statement extension to randomised pilot and feasibility trials.^47^

## Data Availability

No data are available.
